|--|-----------------------------------------------------------------------------------------------------------------------------------------------------------------------------------------------------------------------------------------------------------------------------------------------------------------------------------------------------------------------------------------|
|  | 
rate of 5% and at least 80% power.
 

• ORRs were reported with two-sided 95% exact confidence intervals (CIs), and the number and percentage of patients in each response category were descriptively tabulated. DOR, PFS, RFS, and OS will be analyzed by Kaplan-Meier approach. Safety analyses will be presented descriptively.

 |
|--|-----------------------------------------------------------------------------------------------------------------------------------------------------------------------------------------------------------------------------------------------------------------------------------------------------------------------------------------------------------------------------------------|

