| Study Design       | 
This is a Phase 1b/2, multi-center, open-label, single-arm study. The study will enroll approximately 37-40 patients.
 
In phase 2, Simon's two-stage design was used, in the first stage, 7 patients were to be accrued, if the ORR rate was less than 4/7, the study would be stopped. If not, patient recruitment would continue until the number reached 28, however, further enrollment will be halted if futility is confirmed.
                                                                                                                                                                                                                                                                                                                                                                                                                                                                                          |
| Screening criteria | 
Inclusion Criteria:
 
 
1. Subjects who have fully understood the study and have signed the informed consent form (ICF).
 
2. Male or female, age over 18 years (including 18) old and no more than 75 years old.
 
3. Extranodal NK/T-cell lymphoma confirmed by histopathology examination.
 
4. Refractory and relapsed ENKTCL that has failed the treatment of asparaginase-based chemotherapy or radiochemotherapy.
 
 
Definition of refractory:
                                                                                                                                                                                                                                                                                                                                                                                                 |

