| Sample Size:                             | Approximately 37-40 patients.                                                                                                                                                                                                                                                                                                                                                                                                                                                                                                                                                                                                                                                                                                                                                                                                                               |
| Statistical analysis                     | 
Study Hypotheses:
 
 
• ORR based on investigators for patients treated with sintilimab plus chidamide to be 80% with a one-sided type 1 error rate of 5% and at least 80% power.
 
• Simon's two-stage design was used.
 
• Sample size for phase II of the study was calculated assuming the target ORR of combination treatment to be 80% with a one-sided type 1 error
 
                                                                                                                                                                                                                                                                                                                                                                                                        |

|  |                                                                                                                                                                                                                                                                                                                                                                                         |

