**Approximately 9 to 18 patients are needed for stage Ib.**

- The phase II study adopts the Simon two-stage optimal design method. The main purpose of the research is to use the maximum tolerated dose determined in phase Ib as the recommended dose to preliminarily evaluate the ORR of treatment of chidamide combined with anti-PD-1 antibody in the treatment of refractory and relapsed Extranodal NK/T-cell lymphoma. According to previous studies,  $P_1$  is supposed as 0.8 (expected effective rate) and  $P_0$  as 0.55 (poor effective rate), with  $\alpha=0.05$  and  $\beta=0.8$ . The best two-stage design is (4/7, 19/28). That is, 7 patients were enrolled in the first stage, and if only 4 or fewer patients were effective, the trial was terminated. Otherwise, the trial enters the second phase and 21 more patients will be enrolled. That is, a total of 28 patients will be enrolled in the phase II study. A total of 37 to 46 patients will be enrolled in stage Ib and II. The study loss rate was set at 10% and a total of 40-50 patients will be enrolled. If the number of effective cases in all patients in the two stages exceeds 19, there is an 80% probability that the test drug is effective.

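### The synopsis continues phase II at exactly 4 responses in 7 where Section 10.1 stops it, and the synopsis total of 37–40 does not match Section 10.1

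*Protocol*

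**What the plan says.** The Study Design row of the Protocol Synopsis describes a Simon two-stage phase II with 7 patients first and says that "if the ORR rate was less than 4/7, the study would be stopped"; otherwise accrual goes on to 28. It adds that enrolment will be halted if futility is confirmed, without a number. The Statistical analysis row sets the target ORR at 80% "with a one-sided type 1 error rate of 5% and at least 80% power". The synopsis gives no final cutoff.

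Section 10.1 takes a poor rate of 0.55 and an expected rate of 0.80 and arrives at the design (4/7, 19/28). It explains the first stage as follows: "7 patients were enrolled in the first stage, and if only 4 or fewer patients were effective, the trial was terminated". Success requires more than 19 responders over both stages.

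On size, the synopsis states: "The study will enroll approximately 37-40 patients". Its Sample Size row repeats that range. Section 10.1 adds 9–18 in phase Ib to 28 in phase II to reach 37–46, and then says: "The study loss rate was set at 10% and a total of 40-50 patients will be enrolled". Section 5.1.2 also sets phase II at 28.

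**The concern.** The interim rule is the only numeric futility boundary in the protocol, and it gives opposite answers at one of the likelier interim results. Both statements are current text; the amendment tables list eligibility changes only. If the trial followed the synopsis, it would run a different design from the one whose error rates are claimed. The main loss would be protection against carrying an insufficiently active regimen through to 28 patients. The synopsis total matters because an upper limit of 40 could be reached before the planned phase Ib and phase II cohorts are complete.

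**Working it through.** **Inputs.** p0 = 0.55, p1 = 0.80, n1 = 7, n = 28, success if more than 19 respond (all Section 10.1); one-sided 5% error and at least 80% power (synopsis). Section 10.1 prints β as 0.8; this is read as power 0.80.

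**Formulas.** X is the number of responders among the first 7, and the trial stops if X ≤ r1.
- Early stopping: PET = P(X ≤ r1).
- Probability of declaring success: the sum over x = r1+1 to 7 of P(X = x) × P(at least 20 − x responders among the next 21).
- Expected size: 7 + 21 × (1 − PET).

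**Reproducing the stated design (r1 = 4).** An exhaustive search over n up to 40, with error ≤ 0.05 and power ≥ 0.80, returns (4/7, 19/28) as the design with the smallest expected size at p0. The next best is (5/9, 16/23), with expected size 14.06.
- Type I error at 0.55: 0.2140 × 0.0964 + 0.0872 × 0.1971 + 0.0152 × 0.3413 = 0.0206 + 0.0172 + 0.0052 = 0.043.
- Power at 0.80: 0.2753 × 0.8915 + 0.3670 × 0.9569 + 0.2097 × 0.9856 = 0.803.
- PET at 0.55 is 0.684; expected size is 7 + 21 × 0.316 = 13.6.

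**Synopsis boundary (r1 = 3), same final cutoff.** The only change is that the path through exactly 4 of 7 stays open. P(X = 4) = 35 × 0.55⁴ × 0.45³ = 0.292 at 0.55, and 35 × 0.80⁴ × 0.20³ = 0.115 at 0.80.
- Added type I error: 0.2918 × 0.0389 = 0.0114; total 0.0430 + 0.0114 = 0.054.
- Added power: 0.1147 × 0.7693 = 0.088; total 0.803 + 0.088, or 0.892 unrounded.
- PET at 0.55: 0.684 − 0.292 = 0.392; expected size 7 + 21 × 0.608 = 19.8.

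| | Section 10.1: stop at ≤ 4/7 | Synopsis: stop at ≤ 3/7 |
|---|---|---|
| Type I error | 0.043 | 0.054 |
| Power | 0.803 | 0.892 |
| Early stopping at ORR 55% | 0.684 | 0.392 |
| Expected phase II size at ORR 55% | 13.6 | 19.8 |

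**Totals.** 9 + 28 = 37 and 18 + 28 = 46. A cap of 40 leaves 40 − 28 = 12 places for phase Ib, 6 fewer than its maximum of 18. For the loss step, 37 × 1.1 = 40.7 and 46 × 1.1 = 50.6; dividing by 0.9 gives 41.1 and 51.1.

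**Hypothetical only.** Suppose loss replacement took the analysed phase II number to 31 (28 × 1.1 = 30.8), with the Section 10.1 interim rule and the cutoff of more than 19 unchanged. The second stage would then have 24 patients, and the type I error would be 0.2140 × 0.2991 + 0.0872 × 0.4539 + 0.0152 × 0.6151 = 0.113.

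**The case against.** The excess over 5% is conditional and small. The synopsis gives no final cutoff, so 0.054 comes from joining its interim boundary to the cutoff in Section 10.1. With a cutoff of more than 20 of 28, the synopsis boundary would give error 0.023 and power 0.807, which meets both limits. This objection stands as to emphasis: the contradictory decision and the lost early stopping are the point, and the error rate is secondary. It does not remove the contradiction, because more than 19 of 28 is the only cutoff that the protocol contains.

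A reader might infer three stronger things that the document does not support.
- That the total is given in three conflicting ways, or that 40–50 is an arithmetic error. In Section 10.1, 37–46 and 40–50 are consecutive steps of one calculation, before and after loss, and 40–50 is a 10% increase within rounding. Only the synopsis range conflicts.
- That the loss allowance already inflates the type I error. Sections 5.1.2 and 10.1 fix phase II at 28, and nothing says that 31 patients will be tested against 19. The 0.113 shows what would happen if extra patients were counted; it does not describe the plan.
- That the 10% allowance must therefore be deleted. That would be a design preference, and it would leave the denominator open. Section 10.2 limits its full analysis set to patients with an efficacy evaluation, yet counts patients without a post-baseline assessment as non-responders.

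**Conclusion.** The contradiction is real and should be corrected before the stage 1 decision. At exactly 4 of 7, the synopsis and Section 10.1 require opposite actions, with probability 29% at an ORR of 55% and 11% at 80%. Section 10.1 is internally sound and carries the stated design. Under the synopsis boundary, the chance of stopping after 7 patients at an ORR of 55% falls by 29 percentage points, and expected phase II size rises by about 6 patients. The type I error goes 0.4 points over its limit, provided that the Section 10.1 final cutoff is used. These figures assume independent responses, 28 analysed patients and exact binomial probabilities. The synopsis total is a lesser, separate mismatch: its upper end falls 6 short of the pre-loss maximum of 46.

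**What to change.** In the synopsis, state that phase II stops if 4 or fewer of the first 7 patients respond, and that an ORR of 55% is rejected if 20 or more of 28 respond. Replace 37–40 in both synopsis rows with the Section 10.1 total: 37–46 before loss, with 40–50 shown only if labelled as the range after the 10% allowance. In Section 10.1, state that the cutoff of more than 19 applies to exactly 28 phase II patients. Say which 28 these are, and whether patients lost before assessment count as non-responders or are replaced.

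The synopsis changes are wording only and need no more patients than Section 10.1 already plans. Their effect is that 4 of 7 stops the trial, as Section 10.1 already says. Planned power is then 0.803, not the 0.892 of the looser boundary. Naming the 28 patients needs one decision, to reconcile the two statements in Section 10.2.

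### The protocol gives two different stage 1 stopping rules for phase II, and they order opposite decisions at exactly 4 responders in 7

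*Protocol*

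**What the plan says.** The Study Design row of the Protocol Synopsis sets a first stage of 7 patients and states: "if the ORR rate was less than 4/7, the study would be stopped". Otherwise accrual runs to 28. The same sentence adds that enrolment will be halted if futility is confirmed, without a boundary or a time. The synopsis gives no final success threshold. Its Statistical analysis row sets a target ORR of 80% "with a one-sided type 1 error rate of 5% and at least 80% power".

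Section 10.1 (Calculation of sample size) says: "The phase II study adopts the Simon two-stage optimal design method". The target rate "is supposed as 0.8 (expected effective rate") and the unacceptable rate is set "as 0.55 (poor effective rate"). The boundaries follow: "The best two-stage design is (4/7, 19/28"). The rule is then put in words: "7 patients were enrolled in the first stage, and if only 4 or fewer patients were effective, the trial was terminated". If the trial is not terminated, 21 more patients are enrolled, and success needs more than 19 responders in total.

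**The concern.** In Simon's notation r1/n1 = 4/7 means stop when the number of responders is 4 or fewer. Section 10.1 reads it that way. The synopsis reads the same fraction as a strict inequality, so it stops only at 3 or fewer. That is a different design.

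The two rules agree at every stage 1 result except exactly 4 of 7, where one terminates the trial and the other commits 21 more patients. This is the only numerically defined interim decision in phase II, and it concerns the primary endpoint. The trial is open-label and the protocol does not say which text takes precedence. A choice between the two rules made after seeing 4 of 7 would be a data-driven decision. The stated error rates were derived for one of the two rules and do not automatically carry over to the other.

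**Working it through.** **Inputs.** From Section 10.1: p0 = 0.55, p1 = 0.80, n1 = 7, n = 28, success if total responders exceed 19. From the synopsis: one-sided alpha 5%, power at least 80%. Stage 1 stop: X1 ≤ 4 (Section 10.1) or X1 ≤ 3 (synopsis). Section 10.1 prints β as 0.8; this is read as power 0.80, in line with the synopsis.

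**Formulas.** With X1 ~ Bin(7, p) and X2 ~ Bin(21, p):

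- Probability of early termination: PET(p) = P(X1 ≤ r1).
- Probability of declaring success: Σ over x = r1+1,…,7 of P(X1 = x) × P(X2 ≥ 20 − x). This is the type I error at p0 and the power at p1.
- Expected sample size: EN(p) = 7 + [1 − PET(p)] × 21.

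**Step 1: reproduce the plan's design.** A full search over two-stage designs with n from 10 to 44, alpha ≤ 0.05 and power ≥ 0.80, minimising EN(p0), returns r1/n1 = 4/7 and r/n = 19/28. That is the design in Section 10.1, with stopping at 4 or fewer.

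**Step 2: probability of the disputed result.**

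- At p = 0.55: 35 × 0.55⁴ × 0.45³ = 0.2918.
- At p = 0.80: 35 × 0.80⁴ × 0.20³ = 0.1147.

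**Step 3: contribution of each stage 1 result to declaring success.**

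| X1 | X2 needed | p = 0.55: P(X1) × P(X2 ≥ needed) | p = 0.80: P(X1) × P(X2 ≥ needed) |
|---|---|---|---|
| 4 | ≥ 16 | 0.29185 × 0.03892 = 0.01136 | 0.11469 × 0.76930 = 0.08823 |
| 5 | ≥ 15 | 0.21402 × 0.09636 = 0.02062 | 0.27525 × 0.89149 = 0.24538 |
| 6 | ≥ 14 | 0.08719 × 0.19707 = 0.01718 | 0.36700 × 0.95695 = 0.35120 |
| 7 | ≥ 13 | 0.01522 × 0.34127 = 0.00520 | 0.20972 × 0.98559 = 0.20669 |

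Section 10.1 sums the rows for 5 to 7. The synopsis boundary also includes the row for 4.

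**Step 4: operating characteristics with the same final cut-off (more than 19 of 28).**

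| | Section 10.1 (stop at ≤ 4/7) | Synopsis (stop at ≤ 3/7) |
|---|---|---|
| Type I error at 0.55 | 0.0430 | 0.0430 + 0.0114 = 0.0544 |
| Power at 0.80 | 0.8033 | 0.8033 + 0.0882 = 0.8915 |
| PET at 0.55 | 0.6836 | 0.3917 |
| EN at 0.55 | 7 + 0.3164 × 21 = 13.6 | 7 + 0.6083 × 21 = 19.8 |

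**Step 5: does the synopsis boundary break 5% by itself?** No. If it is paired with a final cut-off of more than 20 of 28, which appears nowhere in the protocol, type I error is 2.34% and power 80.7%. The 5.44% arises from combining the synopsis boundary with the Section 10.1 final cut-off.

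**The case against.** The strongest reply is that Section 10.1 is explicit and correct, in notation and in words, so the intended design is clear and this is one misworded sentence in a summary. On that view the type I error point is overstated for two reasons. The synopsis gives no final cut-off, and a futility boundary has no type I error without one. With 19/28 borrowed from Section 10.1, the excess is only 0.44 percentage points. It can be added that 4 of 7 has a probability of only 11.5% at the ORR the trial expects, and that the synopsis allows enrolment to be halted later for futility.

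Much of this stands. The type I error figure is conditional and small, and the case should not rest on it. The contradiction remains, however. Both sentences are current text, and nothing in the protocol says the body overrides the synopsis. The later futility phrase has no boundary, so it cannot decide the 4 of 7 case. The probability of 29.2% at an ORR of 55% is the relevant one for an early stop meant to protect patients from an inadequate regimen.

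**Conclusion.** The concern holds. The synopsis and Section 10.1 order opposite actions at exactly 4 of 7 responders, a result with probability 29.2% at an ORR of 55% and 11.5% at 80%. Section 10.1 states the Simon optimal design correctly; the synopsis sentence is wrong as written.

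The larger consequence of following the synopsis is lost early stopping under the null: 68.4% falls to 39.2%, and about 6 more patients are treated on average (19.8 − 13.6 = 6.2). The smaller one is a type I error of 5.44% against the stated 5%, which assumes the final cut-off of more than 19 of 28 still applies. All figures assume exactly 7 and 28 evaluable patients, independent responses, and no unscheduled futility stop after stage 1.

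This must be fixed, because it leaves the go/no-go decision undefined at a plausible result.

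**What to change.** Replace the synopsis sentence with the Section 10.1 rule: the study stops if 4 or fewer of the first 7 phase II patients respond; if 5 or more respond, 21 further patients are enrolled, for a total of 28. It would help to add the final criterion (more than 19 responders in 28), so that the synopsis describes the whole design. Either define the later halt for futility or delete it.

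The required change is one sentence and leaves the sample size and final analysis as they are. The boundary then matches the design with type I error 4.30% and power 80.3%. In the same edit, correct the β value printed in Section 10.1 to 0.2; this does not affect the calculation above.

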|  | 
with autoimmune diseases who do not require systematic treatment within two years can be enrolled;
 
 
9. Subjects requiring systemic glucocorticoid therapy or other immunosuppressive therapy for a given condition within 14 days before treatment [allowing subjects to use local, ocular, intra-articular, intranasal and inhaled glucocorticoid therapy (with very low systemic absorption); and allowing short-term (< 7 days) glucocorticoid prophylaxis (e.g., contrast agent overdose) Sensitivity] or for the treatment of non-autoimmune diseases (e.g. delayed hypersensitivity caused by contact allergens);
 
10. In the past five years, patients with other malignant tumors have undergone radical treatment, except for basal cell carcinoma of skin, squamous cell carcinoma of skin, carcinoma in situ of breast and carcinoma in situ of cervix;
 
11. Subjects have major surgery within four weeks prior to enrollment or those who have not completely recovered from any previous invasive operation;
 
12. Uncontrolled hypertension (the systolic pressure > 180 mmHg and/or diastolic pressure >100 mmHg after treatment);
 
13. Active hemorrhagic diseases;
 
14. Begin research on live vaccination (except influenza attenuated vaccine) within 28 days before treatment;
 
15. Human immunodeficiency virus (HIV) infection (HIV positive);
 
16. Patients with active hepatitis B or active hepatitis C. Patients who are positive for hepatitis B Surface Antigen (HBsAg) or hepatitis C Virus (HCV) antibodies at screening stage must pass further detection of hepatitis B Virus (HBV) DNA titer (no more than 1000 copies/mL or 500 IU/mL) and HCV RNA (no more than the lower limit of the detection method) in the row. In addition to active hepatitis B or hepatitis C infections requiring treatment, group trials can be conducted. Hepatitis B carriers, stable hepatitis B (DNA titer should not be higher than 2500 copies/mL or 500 IU/mL) after drug treatment, and cured hepatitis C patients can be enrolled in the group;
 
17. Patients with active pulmonary tuberculosis;
 
18. Known history of hypersensitivity to a similar drug and any excipient in the study drug;
 
19. Pregnant or lactating women;
 
20. Have uncontrollable complications, including but not limited to symptomatic congestive heart failure, uncontrollable hypertension, unstable angina, active peptic ulcer or hemorrhagic diseases;
 
21. Any severe or uncontrolled systematic disease, systematic complication, other severe complicated diseases, or any special condition that might make the subjects unsuitable for the study, or might affect the compliance to the protocol or might cause significant
 
 |

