16. Patients with active hepatitis B or active hepatitis C. Patients who are positive for hepatitis B Surface Antigen (HBsAg) or hepatitis C Virus (HCV) antibodies

at screening stage must pass further detection of hepatitis B Virus (HBV) DNA titer (no more than 1000 copies/mL or 500 IU/mL) and HCV RNA (no more than the lower limit of the detection method) in the row. In addition to active hepatitis B or hepatitis C infections requiring treatment, group trials can be conducted. Hepatitis B carriers, stable hepatitis B (DNA titer should not be higher than 2500 copies/mL or 500 IU/mL) after drug treatment, and cured hepatitis C patients can be enrolled in the group;

17. Patients with active pulmonary tuberculosis;
18. Known history of hypersensitivity to a similar drug and any excipient in the study drug;
19. Pregnant or lactating women;
20. Have uncontrollable complications, including but not limited to symptomatic congestive heart failure, uncontrollable hypertension, unstable angina, active peptic ulcer or hemorrhagic diseases;
21. Any severe or uncontrolled systematic disease, systematic complication, other severe complicated diseases, or any special condition that might make the subjects unsuitable for the study, or might affect the compliance to the protocol or might cause significant interference in safety/ efficacy evaluation of the study drug as judged by the investigator.

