### **5.11.2 Prohibited drugs and non-drug therapies**

Subjects should not receive any other investigative or anti-cancer treatment during the treatment period of this study, including chemotherapy, immunotherapy, biological

therapy, Chinese herbal medicine or endocrine therapy (with anti-tumor activity). Subjects are not allowed to receive palliative radiotherapy (except for relief of pain caused by bone metastases) during the period of receiving the research drug. Short-term or topical use of hormones for clinical conditions such as allergies is allowed. For non-neoplastic diseases, low-dose hormones ( $\leq 10\text{mg}$  of prednisone per day or equivalent hormones) can be used, but the use of glucocorticoids in other studies is not allowed (except for use as an antiemetic drug,  $\leq 2$  times per cycle).

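### Exclusion 10 reaches only radically treated second cancers, so an active, untreated or non-radically treated one is left to investigator judgement

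*Protocol*

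**What the plan says.** Exclusion 10 appears in the Protocol Synopsis and again, with the same wording, in section 4.2: "In the past five years, patients with other malignant tumors have undergone radical treatment, except for basal cell carcinoma of skin". The sentence goes on to except squamous cell carcinoma of skin and carcinoma in situ of the breast and of the cervix.

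Two other provisions bear on the same patients:

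- Exclusion 21 (synopsis and section 4.2) is an investigator-judgement clause: "Any severe or uncontrolled systematic disease, systematic complication, other severe complicated diseases, or any special condition that might make the subjects unsuitable". It also covers conditions that might interfere significantly with the evaluation of safety or efficacy.
- Section 5.11.2 restricts treatment on study: "Subjects should not receive any other investigative or anti-cancer treatment during the treatment period of this study".

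Exclusion 18, also identical in both places, reads "Known history of hypersensitivity to a similar drug and any excipient in the study drug".

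**The concern.** A second-cancer exclusion is there to keep out patients whose other tumor could harm them or confuse the lymphoma outcomes. The tumors most likely to do so are those still present. Exclusion 10 is built the other way round: having been treated with curative intent is the trigger for exclusion. Followed literally, it turns away the patient with the lower risk of confusion and says nothing about the patient with the higher one.

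Response is assessed locally by investigators, and the survival endpoints do not separate deaths by cause. A concurrent second tumor can therefore enter the primary endpoint and both survival endpoints. In a multicenter trial, leaving such patients to judgement also invites different sites to decide differently.

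A smaller point sits in exclusion 18. Joining two kinds of hypersensitivity with 'and' leaves it open whether either one is enough.

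**Working it through.** No arithmetic decides this point, so the wording is applied case by case.

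**Step 1. Exclusion 10 as written, for each kind of second cancer.**

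| Other malignancy at screening | Exclusion 10, literal reading | What else could apply |
|---|---|---|
| Radically treated within five years, not an excepted type | Excluded | Not needed |
| One of the four excepted types, radically treated within five years | Allowed | Exclusion 21, by judgement |
| Active and never treated | Not reached | Exclusion 21, by judgement |
| Treated only non-radically, treatment now finished | Not reached | Exclusion 21, by judgement |
| Under non-radical anti-cancer treatment now | Not reached | Exclusion 21; section 5.11.2 if that treatment were to continue |
| Radically treated more than five years ago, now active again | Not reached | Exclusion 21, by judgement |

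**Step 2. Search for another specific criterion.** Exclusion 1 (NK-cell leukemia) and exclusion 3 (central nervous system lymphoma) concern related lymphoid disease. Exclusion 6 concerns unresolved toxicity of earlier treatment, not a tumor. Exclusion 20 is an open list of uncontrollable complications, but its examples are cardiovascular, ulcer and bleeding conditions and it names no cancer. Inclusion 6 (expected survival over 3 months) would stop only a second cancer that is rapidly fatal. No specific criterion covers the bottom four rows.

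**Step 3. How such a tumor would reach the endpoints.**

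- Inclusion 7 accepts a lesion on FDG uptake and imaging features. Inclusion 3 asks for histology of the lymphoma, not of every lesion followed.
- Section 7.2 has the images read by researchers or radiologists at each center.
- Appendix 2 counts a new lesion as PD.
- Section 10.2 ends PFS at progression or death without restricting the cause, and counts death from any cause in OS.

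**Step 4. Size.** The protocol gives no number for patients with a second cancer, so none is estimated. One patient's response status is worth 1/28 = 3.6 percentage points of ORR in phase II, and section 10.1 asks for more than 19 responders, so 19 fails and 20 succeeds. That holds for any single misclassification, whatever its source. The design values (P0 0.55, P1 0.80, 4/7, 19/28) do not depend on exclusion 10.

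**Step 5. Exclusion 18.** In the same list, exclusions 11, 12 and 16 use 'or' or 'and/or' where either condition is enough, which makes a plain 'and' look deliberate. Against that, sections 3.3, 5.1.1 and 5.1.2 say that patients with SD and PD leave the study. No patient can have both at one assessment, so there 'and' joins alternatives. The protocol's usage is mixed, and the wording is ambiguous rather than wrong.

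**The case against.** The best defense is that exclusion 21 already does the work. It covers uncontrolled disease and anything likely to interfere with evaluating efficacy, which is the harm described here. Section 5.11.2 makes it hard to enroll someone under treatment for another cancer, and inclusion 7 asks for imaging consistent with lymphoma. A sensible investigator would probably not enroll a patient with an active second malignancy.

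This rules out one stronger reading that might be inferred, namely that such patients can enter freely: exclusion 21 is a stated criterion. But it is discretionary. Section 5.11.2 governs conduct on treatment rather than entry, and it does not touch an untreated tumor. Where a specific line on second cancers exists, sites will look there first, and it points the wrong way.

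A reader might also infer that the four exceptions are defective because they carry no treatment condition. On the literal reading they are carved out of the radically treated group, so they carry it already.

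For exclusion 18, a reader might infer that a reaction to a similar drug excludes only when an excipient is also involved, and that Amendment 02, by admitting patients previously given PD-1/L1 antibodies or chidamide, therefore opens the way to re-exposure. That rests on reading 'and' as requiring both. In a list of exclusions the ordinary reading is that either is enough, and the protocol itself uses 'and' for alternatives.

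**Conclusion.** The point holds for exclusion 10. As worded, it excludes only patients whose other malignancy was radically treated in the past five years. An active, untreated or non-radically treated second cancer is not excluded by it or by any other specific criterion, only by judgement under exclusion 21 and indirectly through section 5.11.2.

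Its size is limited and cannot be quantified. The number of affected patients is unknown, and no design figure changes. It would be tempting to conclude that the error could produce a false success on ORR, but the documents do not show a direction: a second tumor read as a new lesion would lower ORR. What can be said is that response, PFS and OS are all exposed, and that the rule, if followed, selects the wrong patients. This rests on taking the sentence literally; if it is a slip of drafting or translation, the sponsor's intent may be sound and only the text needs correction.

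Exclusion 18 is a minor clarification.

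**What to change.** Reword exclusion 10 in the Protocol Synopsis and in section 4.2 so that it also covers other malignancies that are active or have not been radically treated, not only those radically treated in the past five years. The sponsor should confirm the intended look-back period and which tumor types are excepted and on what terms, since the documents do not settle these.

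In the same edit, change 'and' to 'or' in exclusion 18 in both places, so that every site treats either hypersensitivity as sufficient.

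The cost is two lines, each reworded in two places, with the ethics committee review that section 11.1 requires for important changes. No sample size, boundary or analysis changes. The effect on accrual should be small if, as seems likely, sites already keep such patients out by judgement; the documents give no figure to confirm this.
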